## Abstract

**Background:**

Strict compliance with prescribed medication is the key to reducing relapses in schizophrenia. As villagers in China lack regular access to psychiatrists to supervise compliance, we propose to train village ‘doctors’ (*i.e*., villagers with basic medical training and currently operating in villages across China delivering basic clinical and preventive care) to manage rural patients with schizophrenia with respect to compliance and monitoring symptoms. We hypothesize that with the necessary training and proper oversight, village doctors can significantly improve drug compliance of villagers with schizophrenia.

**Methods/design:**

We will conduct a cluster randomized controlled trial in 40 villages in Liuyang, Hunan Province, China, home to approximately 400 patients with schizophrenia. Half of the villages will be randomized into the treatment group (village doctor, or VD model) wherein village doctors who have received training in a schizophrenia case management protocol will manage case records, supervise drug taking, educate patients and families on schizophrenia and its treatment, and monitor patients for signs of relapse in order to arrange prompt referral. The other 20 villages will be assigned to the control group (case as usual, or CAU model) wherein patients will be visited by psychiatrists every two months and receive free antipsychotic medications under an on-going government program, Project 686. These control patients will receive no other management or follow up from health workers. A baseline survey will be conducted before the intervention to gather data on patient’s socio-economic status, drug compliance history, and clinical and health outcome measures. Data will be re-collected 6 and 12 months into the intervention. A difference-in-difference regression model will be used to detect the program effect on drug compliance and other outcome measures. A cost-effectiveness analysis will also be conducted to compare the value of the VD model to that of the CAU group.

**Discussion/implications:**

Lack of specialists is a common problem in resource-scarce areas in China and other developing countries. The results of this experiment will provide high level evidence on the role of health workers with relatively limited medical training in managing severe psychiatric disease and other chronic conditions in developing countries.

**Trial registration:**

ChiCTR-TRC-13003263.

## Background

Schizophrenia affects approximately 0.3% to 0.7% of people at some point in their lives [1], or 24 million people worldwide [2], accounting for an estimated 1.1% of global DALYs (disability-adjusted life years) and 2.8% of global YLDs (years lived with disability) [3]. Approximately three-fourths of people with schizophrenia have ongoing disability due to relapses [4]. Compared with the general population, schizophrenia patients have significantly lower scores in physical and psychological QoL (Quality of Life) domains [5].

According to an epidemiological survey in four provinces in China during 2001 to 2005, the adjusted prevalence of schizophrenia is 7.81 per 1,000; more than half of the patients live in rural China with little or no access to professional psychiatrists [6]. Even when treatment is available to villagers, many remain unaware of, or face barriers in accessing, treatment.

### Drug compliance

Since chlorpromazine was introduced in 1952, antipsychotics have become the principal element of schizophrenia treatment, and compliance is key to reducing relapse. A number of studies outside of China have demonstrated that partial compliance with antipsychotic medication is a common problem and is associated with greater risk of hospitalization [7,8]. In a German study, ‘Needing someone to remind them to take their medication’ contributed to partial compliance in 62% of patients [9]. In a previous unpublished study conducted by our group, only 20.8% of villagers with schizophrenia in Liuyang Municipality were under any kind of supervision of their drug-taking, and less than 50% of schizophrenia patients took their daily medication over the past month, consistent with the results of a study in Qingpu, a municipality near Shanghai, which showed that 60% of patients fail to comply with prescribed treatments [10].

### Project 686

The ‘Management of Major Psychoses Treatment Project,’ funded by the central government and known as Project 686, aims to improve the treatment of severe psychoses by dispensing free medications in rural China, with psychiatric professionals visiting rural communities every two months to dispense antipsychotics to patients. Based on our preliminary data, among the 4,000 Project 686 patients registered in Liuyang Municipality, Hunan Province, as having severe mental disorders -- most of them schizophrenia patients -- only approximately 70% obtained their free antipsychotics in the previous two months, and for those who got medications, no information exists regarding actual use. Despite the availability of free medication, challenges to compliance persist; these include engaging family members in compliance, and the two-month interval between psychiatric visits and dispensation of medications [11].

### Case management and village doctors

Community support services commonly available to psychiatric patients in developed countries include drop-in centers, visits by a community mental health team, facilitated employment [9] and support groups. Intensive Case Management (ICM) is a long-term, community-based package of care for severely mentally ill people who do not require immediate admission. Studies comparing various models of ICM involving a variety of caregivers such as family members, mental health workers, psychiatrists-core teams, and community health workers have demonstrated the benefit of ICM for patients with schizophrenia [12,13], including schizophrenic patients in urban areas of China [14,15]; however, it has been difficult to scale up these models in rural China, mainly due to lack of human resources [16]. It is important to develop rational, targeted, and cost-effective risk-reduction strategies to address this human resources issue.

Evidence indicates that regular visits by psychiatrists have a positive effect on treatment compliance of patients with schizophrenia in rural China [11]. However, it is not feasible to depend solely on such specialists for case management given the large population size versus limited number of psychiatrists in rural China. Lay health counselors (LHCs) have been shown to be effective in the treatment of common mental disorders in low-and middle-income countries (LMICs) [17]. It is plausible that village ‘doctors’ are the most appropriate candidates to serve as LHCs in rural China. Village doctors (VDs), despite their title as ‘doctor,’ are individuals with very basic medical training who provide primary and preventive care to villagers in almost every village in China; because VDs are recruited from among the villagers themselves, they are highly conversant with village residents’ health conditions and concerns. Earlier research on the effects of directly observed chemotherapy on tuberculosis, conducted in 1991, showed that satisfactory treatment adherence and response rates were achieved using VDs as case managers [18].

### Implications of our experiment

This study will integrate a village doctor-assisted case management model into the existing Project 686 sites in rural communities of Liuyang. VDs will receive antipsychotics from psychiatrists every two months, store the medications, manage schizophrenia cases by dispensing medications to patients and their family members every week or every day (both intervention strategies will be tested), counsel patients and family members about the importance of compliance, address concerns raised by patients and family members, and monitor patients for signs of disease and indications of non-compliance. Using a cluster randomized trial (CRT), we will compare the effects of this VD model with the care-as-usual (CAU) model employed in Project 686 in which visiting psychiatrists dispense drugs to villagers every two months, but provide no other services. To the best of our knowledge, this is the first study using VDs as case managers for schizophrenia in China. The proposed study has important implications for improving the management of schizophrenia patients in over 100 communities enrolled in Project 686 in China, and will generate findings as to the effectiveness of involving low level health workers and family members in managing mental disorders common in rural China.

## Research design and methods

### Hypotheses and conceptual model

Hypothesis: Patients in the VD model will have higher rates of drug compliance and greater social function than those in the CAU model with respect to symptom relief, quality of life, hospitalization days and risky behaviors.

Conceptual model: Figure 1 illustrates the conceptual model. In this model, VDs exercise five functions of case management: maintaining patient files; accompanying patients to bimonthly psychiatrist visits; storing and distributing antipsychotics; monitoring drug-taking; and monitoring patients for symptoms.

**Figure 1 F1:**
[figure not shown]
Conceptual model.

## Methods

### Sampling and cluster randomized controlled design

We will conduct a cluster randomized controlled trial involving a sample of rural schizophrenia patients in Liuyang Municipality, Hunan Province, China. Criteria for the sample include:

1. Resided in one of the administrative rural villages of Liuyang Municipality for the past year.

2. Diagnosed by psychiatrist as having schizophrenia.

3. Registered for free medication under Project 686.

Due to our long time working relationship with the local government in Liuyang, they have agreed to assist us in the random selection of villages. A total of 40 administrative villages will be selected out of 318 administrative villages at random. We will use the statistical software package STATA to generate 40 random numbers. All villages will be randomized into two groups (the intervention arm and the control arm) by block sampling (block size = four). The randomization will be based on villages rather than individuals. Due to the nature of our experiment, the allocation will not be blinded for the service providers, patients and interviewers, but those who analyze the data will be blinded for the group information. The co-PI of this project, who is a statistician, will be responsible for the random allocation sequence and the assignment of clusters to interventions.

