### Sample size

To minimize contamination and simplify project management, we will use one-stage clustered sampling. For a two-sided significance level of 0.05 and power of 80%, the sample size is calculated for both the binary variable Drug Compliance (DC) and the continuous variable Drug Compliance Score (DCS), with DC referring to a patient outcome achieving pre-defined compliance or not, while DCS refers to a score anywhere from 0 (no compliance) to 10 (full compliance), calculated as the proportion of the number of drugs actually taken by an individual divided by the number of drugs prescribed for that individual over a given period of time. As our previous study of Project 686 patients with schizophrenia in Liuyang Municipality showed a 50% compliance rate, or DC of 0.5, our calculations were based on the need to detect DC in the range of 0.5 (the current rate) to 0.7 (our hypothesized improvement). In conducting our sample size analysis, we used software developed by the University of Aberdeen, U.K., specifically for clustered randomized trials [19].

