### Sample size with the continuous variable drug compliance score (DCS)

The continuous variable DCS will also be used in our data analysis. Our current research in Liuyang indicates a mean DCR score under Project 686 of 7 out of a total score of 10; for a significance level of 0.05 at a power of 80%, and a conservative ICC of 0.1, 38 villages with a total of 380 individuals will be a sample sufficient to detect an effect as small as an increase of 1 in the DCS score. Given the likelihood of drop-outs, we will include 2 additional villages for a total of 40 containing 400 individuals. Once 40 villages have been selected at random, they will be further randomized into 20 villages in the treatment group and 20 in the control group.

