### Procedures

Following a pilot study (see Section below), 40 villages (excluding the pilot study villages) will be randomly selected in Liuyang Municipality. We will conduct a baseline survey of patients with schizophrenia in the villages, collecting data on social demographics, compliance rates, clinical characteristics, and outcome measures. Researchers will explain the research to participants and obtain written informed consent from both patients and family member. And after the randomization, VDs and family members of patients will receive training and education in the 12-month case management protocol as noted in Section above. Researchers will visit VDs every month during the first three months of the study and every three months thereafter for the remaining nine months of the study, obtaining feedback and giving follow-up instructions, and recording and monitoring VDs’ case management work via questionnaire.

In the CAU model, control villages will continue to receive bimonthly visits by psychiatric professionals, who will dispense free antipsychotics per existing Project 686 protocol. No other interventions will be introduced.

Follow-up interviews will be conducted with patients in both VD and CAU model villages at 6 months and 12 months into the intervention, collecting the same data as that collected at baseline (see below).

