## Statistical methods

### Comparison between VD model and CAU model

T, Chi-square and various kinds of regression tests will be used to compare DCR (binary variable), DCS (continuous variable), and hospitalization (continuous variable) and incidence of risky behavior (binary variable) rates between the VD and CAU models. Repeated analyses of variance will be used to compare psychiatric symptoms and social function (continuous variable) scores between the two groups.

We will use a difference-in-difference regression model with one treatment variable and additional regressors as control variables (see below). Insofar as perfect randomization and program execution are rarely achieved, we make use of an equation with a difference-in-difference Ordinary Least Square (OLS) estimator with additional regressors to estimate population true coefficients. The example below uses DCS as the dependent variable.

$$\begin{array}{l} \mathrm{\Delta DC}S_{i}=\beta_{0}+\beta_{1}\mathrm{VDmode}l_{i}+\beta_{2}{\text{SocialEconDemog}}_{i}\\ \;+\beta_{3}{\text{SeverityIllness}}_{i}+\beta_{4}{\text{FamilyCare}}_{i}+u_{i} \end{array}$$

∆DCS: This is the value of DCSi for the i^th^ individual at the end of the experiment minus the value of DCS_i_ at the start, or the change. DCS is the Drug Compliance Score, a continuous variable ranging from 0-10, with 0 indicating zero compliance and 10 full compliance.

Treatment (VDmodel): This is a binary variable indicating whether an individual is enrolled in the treatment model (VD) or the control group (CAU). Treatment = 1 if an individual is in the treatment group and 0 for individuals in the control.

Social EconDemog: This refers to social, economic and demographic characteristics that can be plugged into the model as additional control variables for analysis.

Illness Severity: This is a composite of variables relating to illness severity such as number of years an individual has been diagnosed with schizophrenia before the start of our program, and days of hospitalization due to schizophrenia over the two years before the start of the program.

β4FamilyCare i: This variable indicates the level of care an individual receives from his or her family.

u_i_: This is the residual of all other determinants of DCS.

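### The t and chi-square comparisons of binary drug compliance ignore its baseline value, and the blocks of four name no balancing variable, although village compliance appears to be measured before the draw

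*Protocol article*

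**What the plan says.** **Allocation.** Under Sampling and cluster randomized controlled design, villages are allocated "by block sampling (block size = four"), and "The randomization will be based on villages rather than individuals". No stratifying or matching variable is named. The section on sample size for the continuous score adds that, once selected, "they will be further randomized into 20 villages in the treatment group and 20 in the control group".

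**Timing.** Procedures states: "We will conduct a baseline survey of patients with schizophrenia in the villages, collecting data on social demographics, compliance rates", among other items. Consent is described next, and then the training that follows randomisation. The order survey, consent, randomisation is implied but not stated outright.

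**Analysis.** Under Comparison between VD model and CAU model: "T, Chi-square and various kinds of regression tests will be used to compare DCR (binary variable"), along with other outcomes. From its label as binary, DCR is read here as DC. The section then gives a difference-in-difference regression on the change in the Drug Compliance Score (DCS) and presents DCS as an example. The Abstract applies that model to drug compliance and other outcomes generally. The article says that the model eliminates pre-programme differences in DCS.

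**Sizing.** "For a two-sided significance level of 0.05 and power of 80"%, with previous Project 686 data that "showed a 50% compliance rate, or DC of 0.5" and a target of "0.7 (our hypothesized improvement"). The calculation takes 10 patients per village, an ICC of 0.1 (called conservative; Table 1 also shows 0.01 and 0.05) and 10% drop-out.

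**The concern.** All 40 villages are selected before allocation. Blocks of four in no particular order then secure the 20:20 split and little else. A village's own baseline compliance, a natural predictor of its later compliance, appears to be in hand at the draw, yet no balancing on it is described. If the primary binary outcome is then compared by t or chi-square test, the baseline is not used there either.

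Two things are at stake. A chance gap of half the target effect would make the DC result hard to read, since part of it would carry through to follow-up. Precision already paid for by the baseline survey would also be left unused.

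**Working it through.** **1. The plan's own sample size.** For 0.5 against 0.7 (mean 0.6), two-sided 0.05 and 80% power, with pooled variance:

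n = [1.96·√(2·0.6·0.4) + 0.8416·√(0.25 + 0.21)]² / 0.2² = 93 per arm.

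The design effect is 1 + 9·0.1 = 1.9. Then 93·1.9 = 176.7 per arm, or 18 villages per arm, 36 in all and 360 patients. Dividing, 360/0.9 = 400. This agrees with the article, and all nine cells of Table 1 reproduce. Forty villages give about 85% power with 10 patients each and 83% with 9 each, so the stated 80% is met without stratification.

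**2. Chance of a baseline gap.** With DC 0.5 and 200 patients per arm, the SE of the baseline difference is √(2·0.25·(1 + 9·ICC)/200).

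| ICC | SE (points) | P(gap > 10 points) |
|---|---|---|
| 0.10 | 6.9 | 14.7% (about 1 in 7) |
| 0.05 | 6.0 | 9.7% (about 1 in 10) |
| 0.01 | 5.2 | 5.5% (about 1 in 18) |

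A beta-binomial simulation gives 13.7%, 8.8% and 5.0%. With blocks formed after ranking villages on baseline DC (ICC 0.1), the SD of the gap falls to 1.5 points, and no gap above 10 points occurred in 20,000 simulations.

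**3. Precision of each analysis.** Let ρ be the correlation of village means between baseline and follow-up. Relative to an unadjusted follow-up comparison (variance 1), a change score has variance 2(1 − ρ) and baseline adjustment has 1 − ρ². The change score beats the unadjusted comparison only if ρ > 0.5, and it is never better than adjustment in large samples. The article gives no follow-up correlations, so three pairs (village/patient autocorrelation) are assumed. Simulated SEs of the effect, in points, at ICC 0.1:

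| Assumed pair | ρ | Blocks | Unadjusted | Change score | Baseline-adjusted |
|---|---|---|---|---|---|
| 0.5/0.3 | 0.40 | arbitrary | 6.86 | 7.51 | 6.36 |
| | | ranked | 6.35 | 6.39 | 6.33 |
| 0.8/0.5 | 0.66 | arbitrary | 6.86 | 5.71 | 5.25 |
| | | ranked | 5.25 | 5.19 | 5.16 |
| 0.9/0.7 | 0.80 | arbitrary | 6.86 | 4.31 | 4.13 |
| | | ranked | 4.26 | 4.10 | 4.09 |

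Ranking lowers the SE by 7–38% for the unadjusted comparison and 5–15% for the change score, but only 0.5–2% once baseline is adjusted for.

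**4. Power for DC.** Simulation of 2,500 trials per setting: 40 villages of 10, ICC 0.1, 10% drop-out, 0.5 against 0.7, village-level analysis, assumed village autocorrelation 0.8 and latent patient correlation 0.3–0.7.

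- Arbitrary blocks, unadjusted t-test: 82–83%.
- Arbitrary blocks, change score: 82–90%.
- Arbitrary blocks, adjusted for baseline DC: 91–95%.
- Ranked blocks with block terms: 89–94%.

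At 0.5/0.3 the unadjusted test has about 83% power, use of the baseline brings it only to about 85%, and the change score has about 70%. With ranked blocks, rejection under the null was 4–5% with block terms but 1.8% when the blocks were ignored.

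**The case against.** The strongest reply is that nothing here is an error. Blocked allocation of villages without a stratifier is valid and unbiased, the sample size does not depend on balance, and the planned power is met. All of that stands. So does the point that baseline use is already planned: the difference-in-difference model is announced for drug compliance generally, and the sentence naming t and chi-square tests also lists regression. The article is also silent on how villages are ordered within blocks, and a condensed article may leave that to the full protocol.

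A reader might therefore infer more than the documents support:

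- **That a 1-in-7 gap is what the design implies.** It holds only at ICC 0.1, which the article calls conservative.
- **That the plan makes no use of baseline compliance.** The difference-in-difference model does use it.
- **That the blocks cause the loss of power.** Nearly all the gain comes from baseline adjustment, with or without ranking.
- **That survey before randomisation is a stated rule.** It is only implied.

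The reply leaves two points unanswered. The t and chi-square comparisons named for the primary binary outcome take no account of a baseline gap. The change score removes the gap but is less efficient than adjustment, and with modest persistence less efficient than making no adjustment. The article's claim that differencing is more efficient rests on determinants of compliance persisting over time.

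**Conclusion.** The point holds as a low-cost improvement, not as a flaw that threatens validity. From the plan's own inputs, a baseline DC gap above 10 points has a chance of about 15% at ICC 0.1, 10% at 0.05 and 5–6% at 0.01. Where the difference-in-difference model is used, the gap is removed; where DC is compared by t or chi-square test, it is not.

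The precision gain is less certain than the balance figures, because it depends on follow-up correlations that the article does not give. Power for DC rises from about 82% to 91–95% at an assumed village autocorrelation of 0.8, but only from about 83% to 85% at 0.5 with patient correlation 0.3. The balancing step also presumes that the survey does come before randomisation.

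**What to change.** 1. **Main change, in Comparison between VD model and CAU model.** State that DC will be analysed at village level, or with a model that allows for clustering, with the village's baseline DC as a covariate. This uses data already collected, costs one degree of freedom in a village-level analysis and gives nearly all the precision gain.

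2. **Optional change, in Sampling and cluster randomized controlled design.** State that the baseline survey and consent are completed in all 40 villages first. Rank the villages by baseline DC, form the ten blocks of four from that ranking, and allocate two villages per arm within each block. This adds balance and little further power. The analysis must then include block or baseline DC, since ignoring it makes the test conservative (null rejection about 1.8%).

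The cost of the second change is that no village can start until the last baseline is in, and that up to 9 degrees of freedom are used if block terms are fitted.

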### Instruments

Four types of statistics will be collected at baseline and at 6 months and 12 months into the study:

Socio-demographic characteristics: age, sex, education level, marital status, work, economic status, domestic situation (living alone, with family, or with friends).

Clinical characteristics: years of illness, number of bed days in psychiatric hospital in previous two years.

Compliance: This is our primary dependent variable measure. The binary variable Drug Compliance (DC) will be recorded by interviewing patients and their family members. We define as ‘compliant’ patients who, over the past month, have taken all pills as prescribed; otherwise, patients are recorded as ‘non-compliant.’ We will report 1-month, 3-month, 6-month and 12-month compliance as the proportion of patients achieving compliance over the total number of patients. In addition, a continuous variable Drug Compliance Score (DCS) will be used to measure medication compliance. The DCS score will be measured by dividing the actual number of pills taken by the total number of pills prescribed multiplied by 10 over a given period of time, with scores ranging from 0 (complete non-compliance) to 10 (complete compliance). For example, if a patient over the past month took 20 pills out of 100 prescribed, his compliance will be (20/100) × 10 = 2 for the past month.

Clinical/outcome measures: Four types of measures will be collected.

Symptoms score: Schizophrenia is often described in terms of positive and negative (or deficit) symptoms. Negative symptoms respond less well to medication [20], particularly to the antipsychotics that are typically used for cases in our research. Therefore, we will concentrate on the positive symptoms as these correlate more strongly with medication compliance. The Brief Psychiatric Rating Scale (BPRS) will be used to evaluate positive symptoms. The BPRS is an 18-item rating scale that has been widely used in psychiatric practice and research in China, and has good to excellent reliability and validity.

Social functions: We will use the global assessment of functioning (GAF) scale, in which a score of 0 to100 is converted to a disability weight ([100-GAF score]/100). Patients with a disability weight of 0.40 or greater are classified as moderately to severely disabled.

Quality of life score: We will use the QALY weights developed by Lenert *et al*. [21].

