Our intervention was designed with these means in mind, with VDs playing a pivotal role in facilitating cooperation among patients, family members, and psychiatrists, while themselves providing essential services in educating patients and their families, supervising treatment (particularly with respect to patients’ drug taking) and monitoring for signs of relapse and other developments requiring referral. Living and working in the same village as patients and their families, VDs are easily accessible to patients and likely have already established a bond of trust. With proper training in case management, their current role as providers of basic medical and preventive care can be expanded to include patient education in, and cooperative treatment and monitoring of, mental illness, thus extending the reach of psychiatry into the rural environment. While our analysis is not sufficiently fine-grained to detect the effect of the various individual strategies listed above on drug compliance, it will deliver substantial data on how VDs function in delivering, coordinating and facilitating a case management protocol in which these strategies are mobilized to improve patient outcomes.

The strength of the proposed RCT is its potential to provide high level evidence on the role of VDs in managing schizophrenia, but the proposal has limitations. Our chief concern has been documenting compliance which, when self-reported by patients, is problematic insofar as patients may be reluctant to report poor compliance. With VDs counting pills, directly observing drug-taking and corroborating compliance with family members, we expect that our study will more likely assess the true treatment situation. A further limitation is that our project piggy-backs on the existing free antipsychotic medication program in Liuyang Municipality; thus, the results may not be fully generalizable to populations in communities where Project 686 has not been implemented. Finally, we must recognize that the Chinese healthcare system has yet to compensate VDs financially for the extra effort involved in providing mental health services. We are hopeful that our research will provide evidence of the public health benefit and cost-effectiveness of employing VDs in the management of serious mental health problems, which may in turn facilitate policy changes in creating system incentives for care-givers who provide these services.

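### Follow-up interviewers are left unblinded for a reason that does not apply to them, exposing the interview-based outcomes to avoidable bias towards the village-doctor arm

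*Protocol article*

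**What the plan says.** Under Sampling and cluster randomized controlled design, the protocol article states that "the allocation will not be blinded for the service providers, patients and interviewers, but those who analyze the data will be blinded", and offers the character of the experiment as the reason. This is a positive statement about masking, so the point does not rest on something the article may have left to a fuller protocol.

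Under Instruments, compliance is the main outcome: "This is our primary dependent variable measure". Its binary form comes from interview: "The binary variable Drug Compliance (DC) will be recorded by interviewing patients and their family members". A patient is compliant only if, over the past month, they "have taken all pills as prescribed; otherwise, patients are recorded as" non-compliant. For the continuous form, "The DCS score will be measured by dividing the actual number of pills taken by the total number of pills prescribed multiplied by 10", and no objective source for the pill number is named. For symptoms, "The Brief Psychiatric Rating Scale (BPRS) will be used to evaluate positive symptoms". Social function is scored on the GAF. Risky behaviour is reported by family members. Hospitalization alone is taken from medical records.

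Under Procedures, the follow-up interviews at 6 and 12 months collect the same data as the baseline survey, which is described before randomization. The same section says: "Researchers will visit VDs every month during the first three months of the study and every three months thereafter". The Discussion concedes that compliance, "when self-reported by patients, is problematic insofar as patients may be reluctant to report poor compliance", and relies on the village doctors' own checks to improve it.

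**The concern.** The stated reason fits the people who give or receive the intervention. A village doctor, a patient or a relative cannot fail to notice who handles the medication. An interviewer delivers no care and could visit a village without being told its arm.

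Knowledge of the arm can act in two ways. For BPRS and GAF it can shift the rating itself. For DC, DCS and risky behaviour it can change how hard the interviewer probes and how an ambiguous answer is coded. The DC rule is all-or-nothing, so one missed pill that is not asked about changes the recorded outcome. If interviewers expect the village-doctor model to work, both routes favour VD.

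What is at stake is how a positive result can be read. The article hopes to provide high-level evidence, and unmasked assessment would leave a rival explanation that no later analysis can exclude.

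**Working it through.** **Inputs from the protocol article.** DC 0.5 (current) and 0.7 (target), two-sided 0.05, 80% power (Sample size). Ten patients per village, ICC 0.1, 36 clusters or 360 patients, 10% drop-out, 400 in total (Sample size with binary DC, Table 1). Twenty villages per arm (Sample size with DCS). **Assumed:** f, the share of truly non-compliant VD patients recorded as compliant. The documents give no value, so a range is shown.

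**1. Reproduce the plan's figure.** Per arm before clustering, with pooled variance under the null:

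n = [1.96·√(2·0.6·0.4) + 0.8416·√(0.5·0.5 + 0.7·0.3)]² / 0.2² = (1.358 + 0.571)² / 0.04 = 93.

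Design effect = 1 + 9 × 0.1 = 1.9. Then 93 × 1.9 = 176.7, so 18 villages per arm, 36 in all, 360 patients, and 360/0.9 = 400. All nine cells of Table 1 reproduce this way. The sample size is not in dispute.

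**2. Spurious difference needed for significance.** With 360 evaluable, the effective number per arm is 180/1.9 = 94.7. With DC 0.5 in both arms, SE = √(0.5/94.7) = 0.0727, and 1.96 × 0.0727 = 0.142. That corresponds to f = 0.142/0.5, or about 28%.

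**3. Chance of a false positive favouring VD.** With no true effect, the recorded DC in the VD arm is p₁ = 0.5 + 0.5f. With p̄ the mean of p₁ and 0.5,

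P = Φ{[(p₁ − 0.5)·√94.7 − 1.96·√(2p̄(1−p̄))] / √(0.25 + p₁(1−p₁))}.

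For f = 10%: (0.487 − 1.384)/0.705 = −1.27, so P = 0.102. For f = 20%: (0.973 − 1.379)/0.700 = −0.58, so P = 0.281.

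| f (assumed) | Apparent difference | Chance of significance favouring VD |
|---|---|---|
| 0% | 0 | 2.5% |
| 5% | 0.025 | 5.3% |
| 10% | 0.05 | 10.2% |
| 20% | 0.10 | 28.1% |
| 30% | 0.15 | 55.2% |
| 40% | 0.20 | 80.7% |

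At f = 10% and 20% the chances are 12.0% and 35.3% with ICC 0.05, and 14.7% and 44.7% with ICC 0.01. With all 400 evaluable and ICC 0.1 they are 10.8% and 30.7%. Errors of 10% in opposite directions in the two arms give an apparent difference of 0.10 and about 28%.

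**4. Does anything else in the plan remove the bias?**
- *Blinded analysts* work on values already recorded.
- *The change-score model* (Statistical methods) subtracts baseline. The baseline survey is described before randomization, so a shift that enters only at follow-up in the VD arm passes in full into β₁.
- *The village doctors' checks* (Discussion) are made by people who deliver the intervention. The Abstract says control patients get no other management or follow-up from health workers, so these checks exist in one arm only and make measurement less alike between arms.

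**The case against.** The strongest reply is that unblinded respondents, and not interviewers, are the main source of error in compliance. DC, DCS and risky behaviour are reports by patients or relatives who know their arm, and the Discussion itself names patient reluctance as the chief worry. This stands. Masking the interviewer reduces bias in these outcomes but cannot remove it, and the figures above show what any differential over-reporting would do, whatever its source.

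It also stands that the article does not say who rates BPRS and GAF. That the interviewers do is inferred from Procedures. Masking would be fragile too, because the respondents know who manages the medication.

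A reader might infer more than the documents support:
- *That every interview outcome rests on the interviewer's judgement.* This fits BPRS and GAF only. The others are elicited and coded reports.
- *That the researchers who visit and instruct village doctors also conduct the outcome interviews.* The article neither equates nor separates the two groups, and staffing is detail that an article may leave out.
- *That the plan declares interviewer blinding impossible.* It only says that it will not be done, and why.
- *That all secondary outcomes would echo the bias.* Hospitalization comes from records and offers a check that does not depend on interviewers.

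None of this supplies a reason for telling the interviewers the allocation.

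**Conclusion.** The point holds as a design choice worth changing. It is not an error in the arithmetic or a contradiction. Interviewers are openly unblinded, the stated reason does not reach them, and no other part of the article provides masked assessment. The case is clearest for BPRS and GAF, given the inference that interviewers rate them, and partial for DC, DCS and risky behaviour.

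The illustration (about 10% and 28% chance of a significant result favouring VD at assumed error rates of 10% and 20%, against 2.5% without bias) rests on no true effect, ICC 0.1 and 360 evaluable patients. It shows that modest differential misrecording matters in a trial of this size. It would be tempting to read it as the bias interviewers will cause or as the gain from masking them. The documents support neither reading, because they give no misclassification rate and no way to separate interviewer error from respondent error.

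**What to change.** Amend only the interviewer clause, and keep the statements that providers and patients are unblinded and that analysts are blinded. Suggested wording:

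> Interviewers at 6 and 12 months will not be told village allocation and, as far as the existing team allows, will not be those who train or visit village doctors. They will ask respondents not to disclose who manages their medication, complete BPRS, GAF and compliance items before any question on services received, and record their guess of the arm.

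Add a sentence saying that masking may be incomplete and that respondent-reported compliance remains open to bias from unblinded respondents.

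The cost is protocol wording and a constraint on who interviews where. The article gives no team size, so how far the roles can be separated is unknown, and the wording allows for that. Some interviewers will be unmasked by patients and families, and the recorded guesses will show how often. The sample size is unchanged. Trial status reports only the pilot under way, so the change can still be made before the main trial.
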